##### Diagnostic decisions: diagnostic effect of LDI and accuracy

In the ‘new diagnostic strategy’ group the diagnostic effect of the introduction of LDI will be assessed on the scanning day by comparing diagnostic decisions of burn clinicians, just before and after the use of LDI.

Possible diagnostic decisions before LDI are:

• Superficial partial thickness burn (no study wound)

• Intermediate burn, the burn wound is not obviously superficial or full thickness (if parts of a burn wound are obviously full thickness, this will be recorded also)

• Deep partial thickness of full thickness burn (exclusion patient from study)

Possible diagnostic decisions after LDI are [12]:

• Superficial partial thickness burn, will heal within 14 days

• Intermediate partial thickness burn, will heal between 14–21 days (the spectrum of an ‘intermediate burn’ is smaller after the use of LDI compared to before the use of LDI)

• Deep partial thickness or full thickness burn, will not heal within 21 days

Accuracy of LDI in our study patients will be checked also. Results of laser Doppler imaging are compared with the reference tests: time of wound healing (from burn date until >95% reepithelialisation) and biopsies. In our study protocol, wounds with a healing potential ≤ 21 (assessed by the LDI) are considered as superficial or intermediate partial thickness and wounds with a healing potential > 21 days are considered as deep partial thickness or full thickness. Only in case of surgery a 3 mm-punch biopsy will be taken as a reference test to assess burn depth [1]: in a superficial burn the basal membrane is partially destroyed; in a deep partial thickness burn the basal membrane is entirely destroyed and the dermis partially destroyed; in a full thickness burn, the dermis is also completely destroyed.

##### Therapeutic decisions: timing of surgery indication, timing of surgery and length of hospital stay

The effect of LDI on therapeutic decisions by the burn clinician will be assessed. The first therapeutic decision is on admittance, the second monitored decision is after 2–5 days (based on clinical assessment or clinical assessment in combination with LDI result). In case of postponement of decision, reason of postponement will be investigated and decision making is followed until wound healing.

The possible therapeutic decisions are:

• Surgery

• Postponement of decision

• No surgery

Differences in therapeutic decisions on the day of randomisation will be analysed.

In case of surgery, differences in timing of surgical decision and timing of surgery (in days after randomisation) between the two diagnostic groups will be analysed.

Differences in length of hospital stay between the two diagnostic groups will be analysed as well.

##### Economic evaluation: total costs and cost-effectiveness

The economic evaluation will be performed from a societal perspective in accordance with the Dutch guidelines for economic evaluation studies [24]. A cost-effectiveness analysis will assess the balance between costs and effects of the new diagnostic strategy compared to the current diagnostic strategy.

Total costs in this study represent direct healthcare costs (inpatient and outpatient medical costs), direct non-healthcare costs (travel costs) and indirect non-healthcare costs (productivity loss). Real medical costs will be calculated by multiplying the volumes of health care use with the corresponding unit prices. Costs will be calculated from randomisation until 3 months post burn. A bottom up approach will be applied (following the micro-costing method of Gold et al. 1996) based on a detailed inventory of all resource used during admittance in one of the Dutch burn centres [25].

Cost prizes will be inventoried in the financial department of one burn centre and will be used for all centres in order to prevent measuring cost differences between burn centres. The costs apply to the financial year 2012.

*Specialized burn care costs* include intervention costs, hospital days, and other variable costs:

• The costs per unit of the LDI scanning will be determined by taking into account the initial investment of equipment, investments during use, maintenance, numbers of years of use, discounting, number of procedures per year and personnel costs.

• Hospital day (both ICU and non ICU) costs will be calculated by multiplying the length of hospital stay by the costs of one day of admission. The cost of re-admittance during follow-up will also be calculated. The costs of a day of admittance are based on a detailed inventory (following the micro-costing method of Gold et al. 1996) of fixed costs only: staffing costs, accommodation, equipment, overhead, food, laundry, and medication [25].

• Variable hospital costs will be identified per patient and calculated by multiplying the volumes of health care use with the corresponding unit prices. The included items are: dressing costs, surgical procedures (material, equipment and personnel costs), diagnostic procedures (bronchoscopy, swabs, laboratory and radiology costs), treatment by allied health professionals, splints, pressure garments, and outpatient visits (staffing and material costs).

Data registration will start on the day of randomisation. Data regarding patients’ baseline characteristics and health-care use will be obtained from patient records and the electronic hospital administration.

*Other healthcare costs and non healthcare costs* will be calculated based on charges as a proxy of real costs [24] with the help of data obtained from patient questionnaires after 3 months. Other healthcare costs include nursing-home and rehabilitation centre, homecare, visits to general physicians and allied health professional outside the hospital. Indirect non-healthcare costs include productivity loss in patients and partners or parents (if applicable), and direct non-healthcare costs include patient travel costs.

To measure the economic impact of LDI in burn care cost-effectiveness will be assessed by calculating the incremental cost-effectiveness ratio, defined here as the costs for the ‘new diagnostic strategy’ (minus savings) divided by the difference in wound healing time (measured from randomisation) between the ‘new diagnostic strategy’ and ‘current diagnostic strategy’. Secondary, a cost-utility analysis will be performed, i.e., as cost per Quality Adjusted Life Years (QALY). The cost-utility ratio can be calculated in patients ≥ 5 years only. In children under the age of 5 years, the EuroQol-5D is not validated and no questionnaires are available that allow the calculation of utility scores [18,19]. Overall utility scores for population-based quality of life (derived from the EuroQol-5D) will be obtained and expressed as QALY’s. QALY’s will be calculated by multiplying the utility of a health state by the time spent in this health state using the Dutch valuation tariff [26]. Policymakers and health economists have proposed that costs varying from €25,000 up to €75,000 per QALY may be considered as acceptable [27]. In accordance with guidelines for differential discounting, effects will be discounted at a rate of 1.5% and costs at 4% per year [24].

In case no differences will be found in wound healing and quality of life, the economic evaluation will be based on a cost-minimisation analysis, that consists of a comparison of total costs in both diagnostic strategies.

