### Sample size

A total of 57.5% of admitted burn patients in the Netherlands is treated conservatively (unpublished data, Dutch Burn Repository R3, 2011). The time to wound healing in patients without surgery is approximately 13 days, this will not change after the introduction of LDI. In the 42.5% of surgically treated patients we do expect an effect on wound healing time, because of an earlier operation. The mean time to first transplantation is 14.0 days post burn, the mean time to wound healing is 5 days after surgery [28], resulting in a mean time to wound healing of 19.0 days. The overall mean time to wound healing for all patients combined is 15.6 days ((57.5%*13+ 42.5%*19)/100).

Petrie et al. describe a reduction of 5.3 days in LOS in patients undergoing surgery, after the introduction of the LDI. As a result, in our population, an overall effect of 2.25 (57.5%* 5.3) days can be expected, with a standard deviation of 5 days. A 2-sided test with an α level of 0.05 and a β level of 0.20 (power 0.80) indicates a required total sample size of 190 patients. We expect a low drop out rate because of a short time to follow up to assess primary outcome (time to wound healing). With a 5% drop out we need a total sample size of 200.

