## Statistical analysis

Data will be primarily analysed according to the intention-to-treat principle. We assume that time to LDI will be equal in both diagnostic groups, as a result of randomisation. Thus, the differences in effects (e.g. time to wound healing) and costs will be assessed from randomisation onwards.

Differences in time to wound healing (numbers of days between LDI and day of > 95% reepithelialisation) and timing of surgery in both diagnostic strategy groups will be analysed with Kaplan-Meier curves and log rank test.

Quality of life (derived from the ItQol-47 and EuroQol-6D), scar quality (assessed by the Cutometer®, Dermaspectometer® and POSAS) and length of hospital stay will be analysed using the independent-sample-t-test (in case of normal distribution) or the Mann–Whitney test (non-normal distribution).

Differences in diagnostic and therapeutic decisions will be analysed with the Chi-square test. Diagnostic accuracy will be assessed by calculating sensitivity and specificity of the LDI compared to the reference test: time to wound healing (in conservative treated patients) or biopsy (in surgical treated patients). In addition, receiver operating characteristic (ROC) curves will be calculated for both diagnostic groups.

Differences in mean costs (after randomisation) will be analysed by the Mann–Whitney test, since healthcare costs are typically highly skewed. Non-parametric techniques (bootstrapping) will be used to derive a 95% confidence interval for the differences in distributions of the costs.

The cost-effectiveness analysis and cost-utility analysis are performed by dividing the differences in average costs by the differences in average effects or utility. In a sensitivity analysis, the impact on cost-effectiveness of statistical uncertainty on the main study outcomes will be determined (uni- and multivariable).

Data analysis will be performed using SPSS-software (Statistical Package for the Social Sciences).

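### The switch to cost-minimisation when no difference is found lets a non-significant result stand in for equal effect in the economic conclusion

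*Protocol article*

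**What the plan says.** The rule is in the protocol article under *Economic evaluation: total costs and cost-effectiveness*: "In case no differences will be found in wound healing and quality of life, the economic evaluation will be based on a cost-minimisation analysis", an analysis "that consists of a comparison of total costs in both diagnostic strategies". Both outcomes, healing and quality of life, have to show no difference before it applies.

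The article does not say how an absence of difference will be judged. It gives no equivalence or non-inferiority margin and no confidence-interval criterion. The inferential tools it names are tests for a difference: log-rank for healing, and a t-test or Mann–Whitney test for quality of life (*Statistical analysis*). The *Sample size* section likewise rests on a superiority comparison: "A 2-sided test with an α level of 0.05", at power 0.80.

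The *Statistical analysis* section describes the cost-effectiveness and cost-utility analyses without repeating the condition. They are obtained by "dividing the differences in average costs by the differences in average effects or utility", and the section adds: "In a sensitivity analysis, the impact on cost-effectiveness of statistical uncertainty on the main study outcomes will be determined". It does not say whether either still supports the conclusion once the switch has been made.

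**The concern.** Cost-minimisation is justified when effects are known to be equal, or have been shown to be close enough to equal. A superiority trial that fails to find a difference has shown neither. If the trigger is read as non-significance, the effect difference is set to zero in the economic evaluation and its uncertainty is removed. The question then becomes which strategy is cheaper.

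This matters because cost-effectiveness is one of the trial's stated aims, and the results are meant to guide whether laser Doppler imaging (LDI) is introduced in Dutch burn care. The article also gives reasons to expect a diluted effect. The *Discussion* foresees a learning effect that shrinks the difference between groups, and the *Sample size* section expects benefit only in surgically treated patients. A real but diluted benefit is the case in which a null test is likely and the switch would remove the benefit from the economic result.

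**Working it through.** **Inputs.** From *Sample size*: a difference of 2.25 days, SD 5 days, two-sided α 0.05, power 0.80, and 190 patients before dropout (200 after 5%). Equal allocation, 95 per arm, is my assumption, because the article does not state the ratio. The model is the article's own comparison of means. The planned healing test is log-rank, so the figures show scale and are not exact operating characteristics.

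**The plan's own figure.** Per arm, n = 2 × (1.96 + 0.84)² × 5² / 2.25² ≈ 77.5, so 78 per arm and 156 in total. The stated 190 does not follow from the stated inputs. The dropout step does reproduce: 190 / 0.95 = 200. In addition, the product printed beside the effect (57.5% × 5.3) is 3.05, whereas 42.5% × 5.3 = 2.25. These are separate matters and the present point does not depend on them. They do explain why two miss probabilities are given below.

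**Precision of the healing comparison.**
- SE = 5 × √(2/95) = 0.725 days.
- 95% CI half-width = 1.973 × 0.725 = 1.43 days (t quantile on 188 df).

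**What a non-significant result leaves open.**
- Observed difference 0: the interval runs from −1.43 to +1.43 days. This is 1.43 / 2.25 = 64% of the target effect in either direction.
- Observed benefit just under 1.43 days: the interval runs from about 0 to 2 × 1.43 = 2.86, about 2.9 days. This exceeds the whole 2.25-day target. The mirror image applies to harm.
- Any observed benefit between 2.25 − 1.43 = 0.82 and 1.43 days is non-significant with the full 2.25 days inside the interval.

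**How often a true 2.25-day benefit is not found.**
- At the stated power: 1 − 0.80 = 20%.
- With 95 per arm and SD 5: 2.25 / 0.725 = 3.10 standard errors. Power is 0.87 (0.873 by the normal approximation, 0.870 by the exact t), so the miss probability is 13%.

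**From a missed healing effect to the switch.** Quality of life must also show no difference, so for a true 2.25-day benefit the 20% and 13% are upper bounds on the chance of switching. The article gives no quality-of-life variance or power, so the joint probability cannot be computed from it. As an illustration only, suppose quality of life truly did not differ and one independent 5% test were used. The figures would then be 0.20 × 0.95 = 19% and 0.13 × 0.95 = 12%. If quality of life truly differed, they would be lower still. A true healing benefit smaller than 2.25 days would be missed more often.

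**The case against.** The strongest replies are these.

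- **The text does not mention significance.** This is correct: the criterion is simply undefined. But with no margin and only difference tests planned, non-significance is the one reading that can be applied. The reply changes the wording of the point and leaves its substance.

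- **The miss probabilities overstate the risk.** They concern healing alone, while the trigger needs two null results. This stands, and they are labelled as upper bounds for that reason. They should not be read as the probability of the switch.

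- **Nothing real is lost.** A reader might infer that benefit or harm would vanish from the trial's findings. The article does not support that. Healing and quality of life are analysed in their own right, and the cost perspective is societal: hospital days, surgery, dressings, outpatient visits and productivity loss all enter. Some consequences of faster or slower healing would therefore appear as costs. What leaves the economic conclusion is the effect difference itself and its uncertainty.

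- **The ordinary analysis already deals with uncertainty.** A reader might infer that the plan ignores the correlation between cost and effect. The article does not say so. It plans bootstrapping for cost differences and a uni- and multivariable sensitivity analysis, and whether resampling is paired is detail an article may leave to the full plan. I make no finding on that. The article does not say, however, that this sensitivity analysis survives the switch.

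- **A ratio is unusable when the effect is near zero.** This is true, and it may be why the switch was written. It is a reason to avoid relying on the ratio, for example by using net benefit, and not a reason to set the effect to zero.

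**Conclusion.** The point holds in this limited form. The article states a rule under which a non-significant result on healing and quality of life would be treated as equal effect in the economic evaluation, with no criterion that could establish equality. Under the article's comparison-of-means model (SD 5, 95 per arm, 1:1 assumed), such a result can coexist with a healing benefit of up to about 2.9 days, above the 2.25 days the trial was sized for, or with harm of similar size. For a true 2.25-day benefit, the chance of reaching the switch is at most 20% at the stated power, or 13% with 190 patients and SD 5.

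It should be fixed, but it does not threaten the trial. It affects a contingent step in the economic evaluation. The primary clinical comparison, the randomisation and the data collected are untouched, and it can be corrected before analysis with no loss of information.

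**What to change.** Delete the sentence that turns the evaluation into a cost-minimisation analysis. State instead that, whatever the p-values for healing and quality of life, the economic conclusion rests on incremental mean costs and incremental mean effects with their uncertainty.

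One direct way is to extend the bootstrap already planned for costs to patient-level pairs of cost and effect. From it, report the two increments with 95% confidence intervals, the cost-effectiveness plane, and net benefit or acceptability curves. For QALYs, in patients aged 5 years or more, the range should include the EUR 25,000 to 75,000 the article cites. For healing, use a range of values per day gained. Net benefit needs no division by the effect difference, so it remains usable when that difference is near zero.

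If the sponsor wishes to keep cost-minimisation, the minimum is to allow it only when equivalence has been shown against margins fixed in advance for both healing and utility.

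The cost is a change of wording and a little extra programming. No extra data are needed.

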### Sample size

A total of 57.5% of admitted burn patients in the Netherlands is treated conservatively (unpublished data, Dutch Burn Repository R3, 2011). The time to wound healing in patients without surgery is approximately 13 days, this will not change after the introduction of LDI. In the 42.5% of surgically treated patients we do expect an effect on wound healing time, because of an earlier operation. The mean time to first transplantation is 14.0 days post burn, the mean time to wound healing is 5 days after surgery [28], resulting in a mean time to wound healing of 19.0 days. The overall mean time to wound healing for all patients combined is 15.6 days ((57.5%*13+ 42.5%*19)/100).

Petrie et al. describe a reduction of 5.3 days in LOS in patients undergoing surgery, after the introduction of the LDI. As a result, in our population, an overall effect of 2.25 (57.5%* 5.3) days can be expected, with a standard deviation of 5 days. A 2-sided test with an α level of 0.05 and a β level of 0.20 (power 0.80) indicates a required total sample size of 190 patients. We expect a low drop out rate because of a short time to follow up to assess primary outcome (time to wound healing). With a 5% drop out we need a total sample size of 200.

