The literature on the accuracy of LDI in burn depth assessment is convincing. However, most studies only report on the accuracy of this technique. The diagnostic and therapeutic impact of the introduction of LDI is often only speculated upon.

There is, to our knowledge, only one retrospective cohort study [4], and one prospective non-randomized study [5] that investigated the therapeutic impact of the introduction of laser Doppler imaging. Petrie et al. reported a lower rate of operative interventions (6.8% before and 2.2% after, p= 0.029) in a pediatric burn population after the introduction of LDI and a reduced length of hospital stay of the surgical treated patients (15.1 days before and 9.8 days after, no p-value). The overall length of stay was 3.4 days in 235 patients before and 2.1 days in 270 patients after the introduction of the LDI [4]. Because of the retrospective nature of this study, other factors than the introduction of LDI alone could be responsible for the therapeutic changes [9]. In the study of Kim et al. [5] the impact of LDI on surgically treated pediatric patients with burns was investigated. The mean time to decision making for grafting procedures was shorter in the LDI group compared to the clinically assessed group (8.9 vs. 11.6 days, p= 0.01). Because of the non-randomised design, it is unclear whether this can be contributed to the LDI or to other differences between the groups.

Thus, current research gives some indications on the diagnostic and therapeutic impact of the LDI in burm care. However, randomised studies in both pediatric and adult patients with burns are lacking.

The introduction of LDI possibly leads to a cost reduction in burn care, by preventing unnecessary surgery [3,4], and reducing length of hospital stay [4]. However, no prospective studies are available on the costs and the possible cost reduction of LDI in burn care, nor are cost-effectiveness studies. Therefore, we can conclude that is it still unclear whether LDI actually influences diagnostic and therapeutic decisions, patient outcomes and costs, and thus adds to the quality of care.

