### Participants

All consecutive patients of any ages with acute burns of indeterminate depth (assessed by the treating clinician), who are seen within 5 days post burn at one of the three burn centres, are eligible.

Inclusion criteria:

• Patients with acute burns of indeterminate depth (=intermediate depth; the burn wound is not obviously superficial or obviously full thickness)

• Outpatient treatment or admission in one of the three Dutch burn centres

• Presentation within 5 days post burn

Exclusion criteria:

• The presence of full thickness wounds, next to intermediate wounds

• Topical treatment/dressings that impair scanning (e.g. hydrocolloid dressings)

• Patients with peri-orbital facial burns, in which the eyes are unable to shield

• Patients or their next of kin if they are under aged or temporary incompetent who can not be expected to give informed consent e.g. because of cognitive dysfunction or poor Dutch proficiency.

• Patients with a TBSA burned > 20%

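### The sample-size paragraph does not follow from its own inputs: the multiplier printed for the 2.25-day effect is the wrong one, and 2.25 days with SD 5 needs 158 patients for power 0.80, not 190

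*Protocol article*

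**What the plan says.** All the inputs stand in the Sample size section of the protocol article.

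- **Shares.** "A total of 57.5% of admitted burn patients in the Netherlands is treated conservatively". These patients are expected to gain nothing from the scan. The remaining 42.5%, who have surgery, are expected to heal sooner because they are operated on earlier.
- **Effect in surgical patients.** The figure is borrowed from a retrospective before-and-after cohort: "a reduction of 5.3 days in LOS in patients undergoing surgery, after the introduction of the LDI".
- **Overall effect and spread.** "an overall effect of 2.25 (57.5%* 5.3) days can be expected, with a standard deviation of 5 days".
- **Total.** "A 2-sided test with an α level of 0.05 and a β level of 0.20 (power 0.80) indicates a required total sample size of 190". A 5% dropout allowance raises this to 200.

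The Participants section defines a different mix of patients from the one behind the 57.5%. The setting is "Outpatient treatment or admission in one of the three Dutch burn centres". Burns must be of indeterminate depth, so obviously superficial and obviously full-thickness burns are both out. The exclusions include "The presence of full thickness wounds, next to intermediate wounds" and a burned surface above 20%. The Statistical analysis section names the log-rank test for the primary outcome.

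**The concern.** This paragraph is the only justification for the size of the trial, and every input needed to check it is printed. Two of its figures fail. The product in the parenthesis uses the share of patients who are expected to have no effect, and the total does not match the effect, SD, alpha and power given beside it. The stated power of 0.80 is therefore not the power that the stated inputs deliver.

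A further question is whether a surgical share taken from all admitted patients applies to those the trial enrols. The expected overall effect is directly proportional to that share, and the paragraph neither justifies nor varies it.

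The figure matters beyond bookkeeping. Under the economic evaluation, a finding of no difference in wound healing and quality of life switches the analysis to cost-minimisation. A null primary result would be read against the stated power, so that power should be right and its main dependency visible.

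**Working it through.** **Inputs (Sample size section).** Conservative share 57.5%, surgical share 42.5%, effect in surgical patients 5.3 days, overall effect 2.25 days, SD 5 days, two-sided alpha 0.05, power 0.80, dropout 5%. The allocation ratio is not stated; 1:1 is assumed.

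**Step 1: the effect.**
- As printed: 0.575 × 5.3 = 3.05 days.
- With the surgical share: 0.425 × 5.3 = 2.25 days.

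The same paragraph weights the two shares correctly in its overall mean healing time: 0.575 × 13 + 0.425 × 19 = 15.55, given as 15.6. So 2.25 is the intended effect and only the printed percentage is wrong.

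**Step 2: attempt to reproduce 190.** For a comparison of two means, n per arm = 2 (1.960 + 0.842)² × SD² / effect².
- Effect 2.25, SD 5: 2 × 7.85 × 25 / 5.0625 = 77.5, so 78 per arm and 156 in total.
- With the t distribution: 78.5, so 79 per arm and **158 in total**.
- After 5% dropout: 156/0.95 = 164.2 and 158/0.95 = 166.3, so 165 to 167.

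Other routes, total for 2.25 days and SD 5 unless stated:

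| Variant | Total |
|---|---|
| One-sided, power 0.80 | 124 |
| One-sided, power 0.90 | 170 |
| Two-sided, power 0.85 | 178 |
| Two-sided, power 0.90 | 208 |
| Mann–Whitney, efficiency 0.955 | 164–166 |
| Mann–Whitney, worst-case efficiency 0.864 | 180–182 |
| 15% non-parametric allowance | 179–184 |
| Effect 3.05 days (printed product) | 86–88 |

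None gives 190. A log-rank calculation with an exponential hazard ratio of 13.35/15.6 (an assumption; 13.35 = 15.6 − 2.25) needs about 1,300 events, so that is not the source either. The dropout step does reproduce: 190/0.95 = 200.

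**Step 3: what 190 does deliver.** With 95 per arm and SD 5, t-test power for 2.25 days is 0.87. A total of 190 gives 0.80 only if the SD is about 5.5 or the effect about 2.04 days. Neither value is stated.

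**Step 4: dependence on the surgical share.** Keep 5.3 days and SD 5, with 95 per arm. The effect is share × 5.3, and the break-even for power 0.80 is 2.04/5.3 = 38.5%. The shares below 42.5% are assumed; the article gives none for eligible patients.

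| Surgical share | Effect (days) | t-test power |
|---|---|---|
| 42.5% (stated) | 2.25 | 0.87 |
| 40% | 2.12 | 0.83 |
| 38.5% | 2.04 | 0.80 |
| 35% | 1.86 | 0.72 |
| 30% | 1.59 | 0.59 |

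All these powers are for a difference in means. They are not powers of the planned log-rank test.

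**The case against.** The strongest defence is that nothing harmful follows. The 57.5% is a slip inside a parenthesis: the 2.25 days is what the article's own logic gives, and 3.05 was not the effect carried forward. The total of 190 errs on the safe side, with 0.87 against a claimed 0.80. All of that stands. It limits the consequence but does not make the stated total or power correct.

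A reader might go further and infer that the trial is underpowered because the surgical share comes from patients it does not enrol. The documents do not support this. Admitted patients are eligible, so the populations overlap. Adding outpatients and excluding full-thickness wounds and large burns would plausibly lower the share, but excluding obviously superficial burns removes conservatively treated patients and raises it. The net direction cannot be settled from the article. A shortfall appears only below about 38.5%, and no share for eligible patients is given.

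A reader might also replace the 5.3 days by the shorter time to the grafting decision in the Background, 11.6 − 8.9 = 2.7 days, which at 42.5% would give 1.15 days and power 0.35. That figure comes from a non-randomised study in surgically treated children, and the article itself says that attribution to the scan is unclear. It is a different proxy, not a correction. The 5.3 days is openly described as a length-of-stay reduction. The 2.7 days can serve as an optional sensitivity scenario at most.

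**Conclusion.** The paragraph is wrong as written on two counts that can be checked from its own figures. The multiplier should be 42.5%, and the effect of 2.25 days stands. On that effect with SD 5, two-sided alpha 0.05 and power 0.80, the total is 158 by t-test (156 by normal approximation), which is 32 fewer than stated; 190 evaluable patients give about 0.87. This rests on 1:1 allocation and a comparison of means, which is what a mean difference and an SD imply. The error is conservative on the stated inputs, so the article's own figures do not show an underpowered trial.

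The surgical share is a caveat, not a demonstrated error. It describes a different mix of patients and could be off in either direction, and power falls below 0.80 only under a share of about 38.5%.

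**What to change.** In the Sample size section:

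1. Replace 57.5% by 42.5% in the product, leaving 2.25 days as it is.
2. Make the total and the power agree. Either state 158 evaluable patients for power 0.80 (167 with 5% dropout), or state that 190 evaluable patients give about 0.87, or give the SD (about 5.5) or effect (about 2.04 days) that actually produced 190.
3. Say that these figures are for a comparison of means, while the planned primary test is log-rank.
4. Report power over a range of surgical shares with the 38.5% break-even, and say that the 42.5% refers to all admitted patients. Use repository data restricted to the eligibility criteria where available. The article cites the repository only for admitted patients, so outpatients and indeterminate depth may not be covered. If so, an openly assumed range is enough.

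Keep 200 patients. The cost is a rewritten paragraph and, where feasible, one query of a data source already in use. Recruitment and the analysis do not change.
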